## Abstract

**Background and objectives:**

Intermittent theta-burst stimulation (iTBS) is a patterned form of excitatory transcranial magnetic stimulation that has yielded encouraging results as an adjunctive therapeutic option to alleviate the emergence of clinical deficits in Parkinson’s disease (PD) patients. Although it has been demonstrated that iTBS influences dopamine-dependent corticostriatal plasticity, little research has examined the neurobiological mechanisms underlying iTBS-induced clinical enhancement. Here, our primary goal is to verify whether iTBS bilaterally delivered over the primary motor cortex (M1) is effective as an add-on treatment at reducing scores for both motor functional impairment and nonmotor symptoms in PD. We hypothesize that these clinical improvements following bilateral M1-iTBS could be driven by endogenous dopamine release, which may rebalance cortical excitability and restore compensatory striatal volume changes, resulting in increased striato-cortico-cerebellar functional connectivity and positively impacting neuroglia and neuroplasticity.

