#### Structural and resting-state functional MRI

Structural and functional MRI analyses will be conducted by two experienced imaging scientists with solid knowledge of advanced volumetric and surface structural procedures and resting-state functional connectivity (rs-FC) analysis. After the MRI data are collected, images will be converted into NIfTI format. Subsequently, a visual inspection will be performed for the detection of artifacts, and they will be manually aligned along the anterior and posterior commissure (AC & PC) with Statistical Parametrical Mapping (SPM12).^3^ Four different analyses will be performed to examine cerebral structural and functional integrity.

Gray matter (GM) volume quantification will be obtained following voxel-based morphometry (VBM) methods using the Computation Anatomy Toolbox (CAT-12, version 12.7) with the current version of SPM12. For this purpose, 3D T1-weighted images will first be visually inspected for artifacts. Subsequently, preprocessing will be performed following standard steps suggested in the CAT-12 manual: (1) bias-field correction; (2) segmentation into GM, white matter (WM), and cerebrospinal fluid (CSF); (3) registration to a standard template using the DARTEL algorithm; (4) normalization of GM images to the Montreal Neurological Institute (MNI) template; and (5) modulation and smoothing of normalized data using an 8 mm FWHM Gaussian kernel. GM volumes of cortical regions of interest will be extracted and corrected for total intracranial volume using the Neuromorphometrics atlas.^4^

Cortical thickness (CT) computation will be obtained using the CAT-12 toolbox, which follows an automated method of tissue segmentation based on the estimation of distances between WM and GM voxels using a projection-based thickness method, including topology correction and spherical mapping. Additionally, individual cortical surface maps will be smoothed with a 15 mm Gaussian kernel to allow intersubject comparisons. Regional CT values will be extracted using the Desikan-Killiany atlas (Desikan et al., 2006).

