Independent component analysis (ICA) of rs-FC data. Resting-state fMRI images will be preprocessed using the Data Processing & Analysis for Brain Imaging tool (DPARSF V4.3).^5^ Preprocessing will include removal of the 10 first functional volumes, slice-timing correction, realignment of the first volume, coregistration, segmentation, spatial normalization to MNI space and spatial smoothing (with a 4-mm FWHM Gaussian kernel). Furthermore, ICA will include the estimation and extraction of brain networks of interest following the infomax algorithm, performed with the Group ICA toolbox of fMRI Toolbox (GIFT) software.

Seed-based rs-FC. Resting-state fMRI data will be preprocessed using the Data Processing & Analysis for Brain Imaging tool (DPARSF V4.3; footnote 5). Preprocessing will include removal of the 10 first functional volumes, slice-timing correction, realignment to the first volume, head-motion correction, coregistration, nuisance covariate regression, spatial normalization to MNI space, spatial smoothing (with a 4-mm FWHM Gaussian kernel), and temporal filtering (0.01 Hz – 0.1 Hz). Seed-to-voxel and seed-to-seed FC values will be computed. The brain regions with significant structural differences between the real and sham iTBS conditions will subsequently be used as seeds to trace the brain regions associated with abnormal FC.

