### Statistical analysis

Before any statistical analyses are performed, the normality of the data distributions of outcome variables and parameters will be assessed using the Shapiro–Wilk test to determine whether parametric or nonparametric statistical tests should be used for the different measures in this study. Subjects will act as their own controls, and the data will be analyzed using both parametric (independent-samples *t*-test) and nonparametric (Mann–Whitney U test) methods, as appropriate. To evaluate the carryover effects, a preliminary test will be performed to test the assumption that the washout phase lasted long enough to completely eliminate a carryover impact. To do this, an independent-samples test will be used to compare the sum of the values measured in the two periods for each subject across the two sequence groups.

In the first step, exploratory analysis of correlations between the clinical response variables and all outcome measures will be conducted. Primarily, correlation analyses will be applied to examine correlations of TMS-EMG parameters with motor, clinical, and neurocognitive variables as well as serum biomarkers and brain structural and functional variables. In a second step, significant correlations across timepoints (i.e., use of baseline variables to predict the clinical response at posttreatment) will be analyzed using stepwise multiple regression models to identify the potential factors predicting the clinical response after iTBS.

For structural MRI and functional (EEG, fMRI) data, individual analysis will first involve the statistical pipeline of each software or toolbox (e.g., SPM12, Fieldtrip, Brainstorm, etc.). Next, advanced statistical analysis will be performed by incorporating clinical, cognitive, neuropsychiatric, serum biomarker, electrophysiological, and neuroimaging information using SPSS 23.0 (IBM, Chicago, IL, United States), R, and custom routines written in MATLAB (MathWorks, Natick, United States). Issues affecting the risk of bias related to missing data in our crossover study will be considered. Initially, all patients with missing outcome data will be removed from the analysis of each data subset. Other strategies for managing missing data, such as the last observation carried forward, will also be used to impute values. The threshold for statistical significance will initially be set at *p* < 0.05. All statistical tests will be two-tailed and adjusted for multiple comparisons.

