## Summary and conclusions

This randomized double-blind sham-controlled crossover protocol study will investigate the neural and behavioral effects of iTBS over the bilateral M1 on idiopathic PD. The present combination of iTBS, cortical excitability measures, structural and functional neuroimaging data, and serum biomarkers represents a powerful approach that enables noninvasive, *in vivo* assessment and modulation of brain excitability, connectivity, and neuroprotection and neuroplasticity across motor and nonmotor brain networks in PD patients. We hypothesize that bilaterally stimulation of the M1 with excitatory iTBS will yield beneficial clinical effects that improve MDS-UPDRS-III scores in the ON medication state (i.e., motor improvement in PD patients) by modulating regionally specific changes in BG-cortical volume as well as by functional connectivity among the BG, cerebellum and cortical regions involved in motor processing. Moreover, we hypothesize that these functional and structural brain changes will be dynamically associated with the neuroprotective and neuroplasticity effects of real M1 iTBS reflected by stabilization of NfL and GFAP levels and by elevation of BDNF levels. Thus, these results may provide supportive evidence that the bilateral M1 is an optimal excitatory stimulation target for treatment among stable PD patients.

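### Two exploratory imaging analyses do not match the striatal hypothesis: regional volumes are specified for cortex only, and the one stated seed rule depends on a significant structural difference

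*Protocol article*

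**What the plan says.** **Hypothesis.** The abstract proposes that iTBS may "restore compensatory striatal volume changes, resulting in increased striato-cortico-cerebellar functional connectivity", and the Discussion repeats this. The Summary and conclusions expects clinical benefit by "modulating regionally specific changes in BG-cortical volume as well as by functional connectivity among the BG, cerebellum and cortical regions".

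**Regional structural measures** (Structural and resting-state functional MRI). For volume: "GM volumes of cortical regions of interest will be extracted and corrected for total intracranial volume using the Neuromorphometrics atlas". For thickness: "Regional CT values will be extracted using the Desikan-Killiany atlas".

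**Seed-based connectivity** (same section). Seed-to-voxel and seed-to-seed values will be computed, and then: "The brain regions with significant structural differences between the real and sham iTBS conditions will subsequently be used as seeds". No other seed and no fallback is named.

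**Other planned routes.** The volume analysis starts from whole gray matter: "Gray matter (GM) volume quantification will be obtained following voxel-based morphometry (VBM) methods". Under Statistical analysis, for structural and functional data, "individual analysis will first involve the statistical pipeline of each software or toolbox (e.g., SPM12, Fieldtrip, Brainstorm, etc". A separate group independent component analysis (ICA) extracts networks of interest, which are not named.

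**Status.** Table 1 lists structural MRI and resting-state fMRI as exploratory outcomes.

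**The concern.** The structure at the centre of the hypothesis is missing from the only regional volumes that the article specifies. Cortical thickness cannot fill the gap, because the striatum has no cortical thickness. The Statistical analysis section then correlates brain variables with TMS-EMG, clinical and serum variables and enters significant correlations into regression models. No striatal or basal ganglia regional value is specified for that step.

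The seed rule makes one exploratory analysis depend on another. Connectivity can change without a detectable volume change, and the structural comparison uses a scan on the eighth day after five sessions. If the hypothesised circuit shows no significant structural difference, the seed analysis as stated does not examine it. An empty result would then say nothing against the hypothesis, and a seed elsewhere would not test it.

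**Working it through.** **Step 1: hypothesis against specified analysis.**

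| Element of the hypothesis | Regional measure specified | Other route in the article |
|---|---|---|
| Striatal / basal ganglia volume | None; volumes are cortical and thickness is cortical | Voxel-wise morphometry over gray matter; no contrast named |
| Connectivity of basal ganglia, cerebellum and motor cortex | Seeds only where the structural difference is significant | ICA; networks not named |

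Because the extracted regional values are cortical, a striatal seed could come only from a voxel-wise finding.

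**Step 2: how often would a truly changed region become a seed?** The article gives no figure for the imaging analyses, so there is nothing to reproduce. What follows is an illustration.

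Inputs from the article (Recruitment and sample size; Statistical analysis):
- 24 patients, two-sided 0.05, tests adjusted for multiple comparisons by an unnamed method.
- About 20% drop-out: 24 × 0.80 = 19.2, so 19 completers.

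Assumptions:
- Bonferroni over m = 50 or 100 regions.
- A true change d of 0.5 or 0.64 SD of the within-patient real-sham difference. The value 0.64 is what 21 patients at 80% power imply for the clinical endpoint; it is a yardstick and says nothing direct about gray matter.

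Formula: power = P(T > c), where T is noncentral t with n − 1 degrees of freedom and noncentrality d√n, and c is the two-sided critical value at 0.05/m.

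Worked example, n = 24, d = 0.5, m = 50: noncentrality = 0.5 × √24 = 2.449; alpha = 0.05/50 = 0.001; c = 3.768; power = 0.132.

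| n | d | m = 50 | m = 100 |
|---|---|---|---|
| 24 | 0.50 | 13.2% | 9.0% |
| 24 | 0.64 | 30.3% | 22.8% |
| 19 | 0.50 | 7.8% | 5.0% |
| 19 | 0.64 | 18.3% | 12.8% |

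Using n − 2 degrees of freedom, as in a two-sequence crossover model, changes each figure by less than one percentage point.

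**Step 3: sensitivity.**
- Fewer regions: with m = 10 and n = 24, the figures are about 28% (d = 0.5) and 52% (d = 0.64).
- Several changed regions: with five truly changed, independent regions, P(at least one passes) = 1 − (1 − p)^5. For d = 0.5, 1 − (1 − 0.090)^5 = 0.38 and 1 − (1 − 0.132)^5 = 0.51. For d = 0.64, 1 − (1 − 0.228)^5 = 0.73 and 1 − (1 − 0.303)^5 = 0.84. Correlation between regions would lower these.

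**The case against.** The strongest reply is that the article plans more than these two steps. Morphometry covers all segmented gray matter and SPM12 statistics are planned, so a voxel-wise test can reach the striatum and could supply a striatal seed. Table 1 lists global and regional gray matter volume without limiting it to cortex. ICA tests connectivity without a seed or a structural result. The seed paragraph does not say that structurally different regions are the only seeds. A full protocol may name contrasts and networks, and choosing seeds from structural findings is a recognisable exploratory choice.

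Most of this stands, and it limits the point. A reader might infer that the imaging plan as a whole cannot test its own hypothesis, or that connectivity of M1, striatum and cerebellum would go untested. The documents do not support that, because the morphometry and ICA routes exist. A reader might also infer from the table that the likeliest outcome is no seed from any truly affected region. The figures do not show that: they apply to one given region, and with five changed regions the chance of at least one seed can pass 50%. Nor is a chance seed a large worry if the stated multiplicity adjustment is applied at this step, since Bonferroni holds the chance of any false seed to about 5% under the null.

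The reply does not remove the mismatch in what is written. The extraction sentence states cortical regions, and the seed sentence states a rule. These are choices already fixed in the text, and neither fits the stated circuit.

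**Conclusion.** The point holds for two exploratory analyses: the regional-volume extraction and the seed-based connectivity analysis. The first specifies no striatal or basal ganglia region. The second, by its only stated rule, would miss a connectivity change in the hypothesised circuit that lacks a significant structural counterpart.

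The text comparison carries this conclusion. The power figures (about 9-13% at 0.5 SD and 23-30% at 0.64 SD for one given region, 24 patients) only illustrate how strict the structural condition can be, and they rest on assumed effect sizes, region counts and Bonferroni correction. That structurally derived seeds are the only seeds is an inference from silence: no others are named, and none are excluded.

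Severity is minor. The primary outcome is MDS-UPDRS, and no efficacy conclusion depends on these analyses.

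**What to change.** In Structural and resting-state functional MRI:

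1. Add striatal (putamen, caudate), other basal ganglia and cerebellar volumes to the atlas extraction, with the same correction for total intracranial volume.
2. Fix seeds in advance from the hypothesis: both M1 hand areas, putamen, caudate and a motor cerebellar region. Keep structurally derived seeds as an additional analysis.
3. State which voxel-wise contrast and which ICA networks address the hypothesised circuit.

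Cost: wording only, on scans already planned. The small downside is a few more comparisons to adjust for.

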#### Quantification of serum brain biomarkers

Serum quantification of protein biomarkers will be determined by a biologist and a laboratory support technician with training on structured protocols that will include extensive supervised practice and performance-based certification. All measurements will be assessed via ultrasensitive single molecule array (Simoa™) technology through the SR-X Instrument (Quanterix Corporation, MA, United States). Serum NfL and GFAP levels will be measured using the Neurology 2-Plex B assay, and BDNF levels will be measured using the BDNF Discovery kit (Quanterix, Corporation MA, United States). All data will be analyzed according to the manufacturer’s instructions and recommendations for blood biomarkers.

### Statistical analysis

Before any statistical analyses are performed, the normality of the data distributions of outcome variables and parameters will be assessed using the Shapiro–Wilk test to determine whether parametric or nonparametric statistical tests should be used for the different measures in this study. Subjects will act as their own controls, and the data will be analyzed using both parametric (independent-samples *t*-test) and nonparametric (Mann–Whitney U test) methods, as appropriate. To evaluate the carryover effects, a preliminary test will be performed to test the assumption that the washout phase lasted long enough to completely eliminate a carryover impact. To do this, an independent-samples test will be used to compare the sum of the values measured in the two periods for each subject across the two sequence groups.

In the first step, exploratory analysis of correlations between the clinical response variables and all outcome measures will be conducted. Primarily, correlation analyses will be applied to examine correlations of TMS-EMG parameters with motor, clinical, and neurocognitive variables as well as serum biomarkers and brain structural and functional variables. In a second step, significant correlations across timepoints (i.e., use of baseline variables to predict the clinical response at posttreatment) will be analyzed using stepwise multiple regression models to identify the potential factors predicting the clinical response after iTBS.

For structural MRI and functional (EEG, fMRI) data, individual analysis will first involve the statistical pipeline of each software or toolbox (e.g., SPM12, Fieldtrip, Brainstorm, etc.). Next, advanced statistical analysis will be performed by incorporating clinical, cognitive, neuropsychiatric, serum biomarker, electrophysiological, and neuroimaging information using SPSS 23.0 (IBM, Chicago, IL, United States), R, and custom routines written in MATLAB (MathWorks, Natick, United States). Issues affecting the risk of bias related to missing data in our crossover study will be considered. Initially, all patients with missing outcome data will be removed from the analysis of each data subset. Other strategies for managing missing data, such as the last observation carried forward, will also be used to impute values. The threshold for statistical significance will initially be set at *p* < 0.05. All statistical tests will be two-tailed and adjusted for multiple comparisons.

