Spectral estimates of the relative power of each frequency band during baseline and post-iTBS at any electrode will then be obtained for each participant by subtracting the log-transformed band power during the eyes-closed and eyes-open baseline conditions from the log-transformed band power after treatment, according to the following formula:

Relative frequency band power (*i*) = log (power_i, posttreatment_) – log (power_i, baseline_).

Finally, synchronization measures, such as imaginary coherence (Avena-Koenigsberger et al., 2018) with sensor and source EEG space, will be calculated by obtaining different graph theory metrics to determine the association between graph theory metrics of EEG resting-state brain connectivity and real or sham iTBS treatments. Graph theory measures will be calculated with the igraph package^1^ for the R toolbox (R Core Team, 2018) and Brainstorm software (Tadel et al., 2011; Niso et al., 2019). Resting-state EEG power and EEG connectivity analysis will also be performed by parametric and nonparametric permutation tests to calculate the pre vs. post and real vs. sham differences.

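### A Shapiro–Wilk test on the outcome values, rather than on within-patient differences, picks the t-test or the rank test, and no default is named for the primary outcome

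*Protocol article*

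**What the plan says.** The Statistical analysis section opens with the rule. Before any analysis, the outcome variables and parameters are checked for normality, which is "assessed using the Shapiro–Wilk test to determine whether parametric or nonparametric statistical tests should be used", measure by measure. The two branches follow directly: an independent-samples t-test, or "nonparametric (Mann–Whitney U test) methods, as appropriate".

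The same paragraph says "Subjects will act as their own controls", so a within-patient comparison is intended. For carryover it names a derived per-patient quantity and would "compare the sum of the values measured in the two periods for each subject across the two sequence groups". It names no derived quantity for the normality check or for the treatment comparison.

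The section on recruitment and sample size describes a 2 × 2 crossover at two-sided 0.05 and 80% power. It needs at least 21 patients, plans 24, and takes UPDRS-III motor change as the primary endpoint. No section names a default test for that endpoint.

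**The concern.** Each patient is measured under both real and sham stimulation. The patient's own level is common to both phases and cancels from the phase difference. A t-test on that difference needs the differences, or the residuals of the equivalent model, to be roughly normal. It does not need the scores themselves to be normal.

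The shape of the scores mostly reflects which patients were enrolled, here Hoehn and Yahr II–III in the ON state. A check on the scores can therefore reject when the t-test is sound, and can pass when the differences have heavy tails.

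What is at stake is which test decides the primary endpoint, and with it the effect measure. A t-type analysis gives a mean difference in MDS-UPDRS points. Mann–Whitney U, as named, does not give one by itself. The article states this rule outright, so it is not a detail left to an analysis plan.

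**Working it through.** **The plan's own figure.** The 21 patients cannot be recomputed, because no effect size or standard deviation is given. It can be solved backwards. For n = 21, two-sided 0.05 and 80% power, the noncentral t with noncentrality d√21 gives d = 0.643, in units of the SD of the within-patient difference. With 24 patients the noncentrality is 0.643 × √24 = 3.15 on 22 degrees of freedom, which gives about 85% power for the t-test. This effect is used below.

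**Why the patient level cancels.** Write the score of patient i in phase p as y(i,p) = b(i) + phase effect + treatment effect + e(i,p). The difference is d(i) = y(i,1) − y(i,2), in which b(i) no longer appears. If b has share 0.8 of the variance and skewness s, the raw score has skewness 0.8^1.5 × s = 0.716 s. That is 0.72 for s = 1.0 and 1.00 for s = 1.4. The differences have skewness 0 whenever the errors e are normal.

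**Simulation.** From the document: 24 patients and two sequences, taken as 12 per sequence under the 1:1 allocation. Assumed: intraclass correlation 0.8 and the distribution shapes. The raw-score check applies Shapiro–Wilk at 0.05 to the values in each condition and moves to ranks if either is rejected. The comparison check applies it once to the phase differences with sequence means removed. Both tests are then run on the phase differences between sequences.

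| Severity; within-patient error | Raw check moves to ranks | Check on differences moves to ranks | Power, fixed t | Power, fixed ranks | Power, pretest rule |
|---|---|---|---|---|---|
| Normal; normal | about 10% | about 5% | 86.6% | about 82% | 86.2% |
| Skewness 1.0; normal | about 31% | about 5% | 84.6% | about 82% | 83.7% |
| Skewness 1.4; normal | about 47% | about 5% | 85.6% | about 82% | 83.9% |
| Normal; t with 3 df | about 14% | about 27% | about 88–89% | about 93% | about 91% |

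The first row shows 10% rather than 5% for the raw check because two conditions are each tested at 5%.

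**Power cost of the pretest rule against a fixed t-test, normal errors.** 86.6 − 86.2 = 0.4 points, 84.6 − 83.7 = 0.9, and 85.6 − 83.9 = 1.7. As a rough check, the t-test has about 3.5 points more power than ranks here (85.5% against 82%). Then 0.10 × 3.5 = 0.35 and 0.47 × 3.5 = 1.6.

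**Verdicts.** With the effect present, the t-test and the rank test disagreed on significance in about 5–7% of trials.

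**Sensitivity to the assumptions.** A second set of runs used intraclass correlations of 0.6 and 0.8. With normal errors the raw check moved to ranks in 33–53% of trials for skewed severity and 9–38% for bimodal severity. The check on differences, made separately in each sequence, did so in 8–10% whatever the patient mix. Type I error of the two-stage rule was 4.3–5.9%, with simulation error of about one point.

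**The case against.** The strongest reply is that the article never says the raw scores are what is checked. It speaks of outcome variables and parameters, and the sample-size text describes the primary endpoint as motor change. If the tests are run on per-patient phase contrasts and that contrast is what is meant by the outcome variable, the check is aimed correctly. If the tests are run on the scores as measured, the check and the test look at the same values, and the fault is lost pairing, a separate matter. The mis-aiming arises when a check on scores is followed by a within-patient test.

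This stands in part. The plain reading of the text is the measured values, and the section defines a per-patient quantity for carryover but none here. A pre–post change would remove much of the patient's own level, so patient mix would matter less. It would still not be the difference between phases. Under every reading, the trial's own data choose between two tests and no default is named for the primary outcome.

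It is also fair to say that a two-branch rule stated beforehand is not a free choice made after seeing results. That is accepted. The objection here is to what the rule looks at.

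Finally, a fixed t-type analysis is not best everywhere. With heavy-tailed differences it has about 88–89% power, against about 91% for the pretest rule and about 93% for ranks. This is a true cost of the fix.

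**Conclusion.** The point holds, at moderate weight. The article states a pretest that, on its plain reading, examines the wrong quantity for a crossover and leaves the primary test to depend on it. With exactly normal differences and an intraclass correlation of 0.8, the raw-score check moves to ranks in about 10% of trials with normal severity and 31–47% with skewed severity, against about 5% for a check on residual differences. With heavy tails it notices in about 14% against 27%. These rates rest on assumed shapes and an assumed correlation, since the document gives no variance figures.

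A reader might infer three stronger things that the document and the calculations do not support:

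- **Inflated false-positive rate.** Type I error stays near 5%.
- **Serious loss of power.** Against a fixed t-test the loss is under 2 points with normal errors, and with heavy tails the rule gains slightly.
- **Different tests at different visits of one score.** Each phase has four post-treatment motor evaluations and nothing ties them to one test, so this is possible. It is not stated, and the wording can mean one choice per measure. If the check were repeated at each visit, switching would also occur with differences (31–33% of trials with normal errors). Re-aiming the check would therefore not cure it; naming one test would.

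**What to change.** Delete the Shapiro–Wilk rule. Before unblinding, name one primary analysis of MDS-UPDRS-III on the within-patient contrast. This can be a linear model with patient, phase and treatment, or the equivalent t-test comparing phase differences between the two sequences. Report the treatment estimate in points with its 95% CI whatever any normality check shows, and use residual plots or tests only as diagnostics.

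Pre-state one sensitivity analysis, either a permutation test within the design or a rank test on the phase differences, with a Hodges–Lehmann estimate and interval. This covers the heavy-tailed case, where the t-type analysis has less power.

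The cost is a few sentences of analysis wording and no new data. The article reports recruitment as ongoing, with thirteen patients enrolled and four crossed over, so on that status the change can still be made before unblinding.
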